**III Research plan, methods, and implementation**

The study population is adult patients treated for coronavirus infection in intensive care units of the HUS area who meet the inclusion criteria and have no contraindications to the study.

**Admission criteria:**

- 18 years old

- the language of business is Finnish or Swedish. For the neuropsychological part of the study, only persons whose business language is Finnish can be included because there are no validated versions of tests for Finnish-Swedes and the test results are very language sensitive. In all other sub-investigations, persons whose business language is Swedish can also be included.

-is in intensive care in one of HUS's intensive care units due to a severe coronavirus infection

-Is involved in the RECOVID study

**Exclusion criteria:**

-pregnancy

- a significant neurological disease diagnosed before the coronavirus infection, such as a severe one

the aftermath of a brain injury or cerebrovascular accident

-sensory impairment

- memory disorder

-Parkinson's disease

-disability

Section-specific exclusion criteria, if any, are listed in connection with the description of each study section. The assumed number of patients is around 100-150. Patients are identified after intensive care using a registered COVID-19 diagnosis from the intensive care quality database, after which they are contacted and asked to participate in the study. Patients are sent a *Patient and Next of kin Research Information Sheet* and a consent form with the contact information of the research team for further details. For the continuation of the study, new information about the subject and consent forms will be sent to the subjects by post, or their consent will be asked when meeting them at the follow-up clinic. Among the research subjects, there are only people who use Finnish as their business language, so the research documents for further research have only been prepared in Finnish.

Control patients are recruited through a newspaper advertisement and with the help of social media. Control patients are persons with a confirmed coronavirus infection whose severity of illness did not require intensive care, but the disease was contracted at home (N=50). Another control group, patients who received treatment for coronavirus infection in a hospital bed ward (N=50), will be identified to ask for consent from those who receive/are receiving an invitation to a follow-up organized by the lung disease clinic. Separate written consent to participate in the study is requested from the control persons.

We also recruited 50 control subjects who had not had a COVID-19 infection. The table below shows the sub-studies of the study in which these so-called non-Covid controls will be compared to other subjects. The aim is to find non-Covid controls by September 14, 2020, from the close circle of the subjects who gave their consent to the study so that they would be as similar as possible to the subjects treated in the intensive care unit in terms of socioeconomic status and educational level. In practice, the subjects are asked at the follow-up clinic if there are people in their close circle who have not had COVID-19 and whom they would estimate would be willing to participate in the study. They will be forwarded the contact information of the research team so that they can express their interest in the research if they wish. After this, possible non-COVID-19 control subjects will be sent the study information and a consent form in a return envelope.

If enough non-COVID controls are not found through this method, they can also be found among the staff of the University of Helsinki from different professional groups by announcing the recruitment on the University's intranet pages. The aim is to obtain controls from different age and professional groups so that the educational level does not differ significantly from the subjects (who were in intensive care due to Covid).

Patients who give their consent will receive an invitation to come for examination and clinic visits six months after intensive care. Before visiting the outpatient clinic, three months after the disease, the research patients are given a short neurological, and a neuropsychological survey by phone and two questionnaires are mailed to them. More extensive inquiries are made at two separate visits six months after intensive care. The attached table shows the time points and the maps planned for them. At Uppsala Academic Hospital and Oslo University Hospital (if possible), a part of the table will be performed for the corresponding patient groups for the mentioned tests, and the data for them will be combined. mRS, RAND-36, MOCA, and IQCODE tests are conducted in Uppsala. Control patients for the MRI study are searched for using a newspaper advertisement, after which, based on contact, they are asked for informed consent to participate in the study.

Table 1. Tests used in the study, division of labor, time points, and subjects number in HUS. *=Separate consent

| Helsinki |  |  |  |
| --- | --- | --- | --- |
| Three months | Who makes | Number of patients | Controls |
| Registration of clinical data from patient records (neurological symptoms and examinations during intensive care, delirium, duration of treatment and procedures, background information) | [name] [name] [name] [name] [name] | 100-150 | 50 who were in ward treatment |
| Telephone interview: modified Rankin Scale (mRS) | [name] [name] [name] [name] [name] | 100-150 | 50 inpatients + 50 COVID patients sick at home |
| Telephone interview: Montreal Cognitive Assessment (T-MoCA) | -“- | 100-150 | 50 inpatients + 50 COVID patients who got sick at home + 50 non-COVID controls |
| Behavior Rating Inventory of Executive Function, adult version (BRIEF-A) +BRIEF Informant version ABNAS Neuropsychological questionnaire | by post | 100-150 | ,, |
| Six months | by post |  |  |
| RAND-36 | by post | 100-150 | 50 inpatients + 50 COVID patients sick at home 50 + non-COVID controls |
| MFI-20 | by post | 100-150 | ,, |
| HADS | by post | 100-150 | ,, |
| Informant Questionnaire on Cognitive Decline (IQCODE-CA) | by post | 100-150 | 50 inpatients + 50 COVID patients who got sick at home |
| Behavior Rating Inventory of Executive Function, adult version (BRIEF-A) +BRIEF Informant version | By mail (or NPS in connection with the study) | 100-150 | 50 inpatients + 50 COVID patients sick at home + 50 non-COVID controls |
| Background information | visit (see Visit 1 below) | 100-150 | ,, |
| modified Rankin Scale ( mRS) | visit | 100-150 | ,, |
| Montreal Cognitive Assessment ( MoCA ) | visit | 100-150 | ,, |
| National Institute of Health Stroke Score (NIHSS) | visit | 100-150 | ,, |
| CFS-9 ( clinical frailty scale ) | visit | 100-150 | ,, |
| Olfactory screening test | visit | 100-150 | ,, |
| Follow-up of lung diseases (with the patient's consent, data retrospectively for comparison) | Lung x-ray, spirometry, and diffusion capacity measurement, telephone interview (skin and allergy hospital) | 100-150 | Data from clinical lung function tests of 50 patients who were in ward treatment |
| **Visit 1** |  |  |  |
| Neuropsychological research [name] | Student /[name]/[name]/ [name]/ [name] | 100-150 | 50 inpatients + 50 COVID patients sick at home + 50 non-COVID controls |
| Laboratory samples (immunology) | HUSLAB | 10-50 |  |
| Brain MRI (ULS) | HUS imaging [name], [name] , [name] | 50 who were in intensive care (at least 30) | 50 inpatients + 50 COVID patients sick at home + 50 non-COVID controls |
| Smell and taste testing | Research nurse | 50 who were in intensive care | -”- |
| **Visit 2** |  |  |  |
| 6-minute walk test | Research nurse, physiotherapist [name] , ERL [name] , LK [name] (6mwt) | 100-150 |  |
| Spirometry and diffusion capacity, meeting with the intensive care physician, reporting the results, and discussing possible further plans | [name], LK [name], [name], / [name] / [name] | 100-150 |  |
| Laboratory samples Fibrosis/inflammation markers Neurofilament + ApoE alleles* | MMP and TIMP-1 analyzes [name] TAU [name] , [name] (University of Gothenburg) [name] | 100-150 | 50 inpatients + 50 COVID patients sick at home + 50 non-COVID controls |
| Method testing of antibody assays Hyyttek , CAT= calibrated automated thermogram , microvesicles, PF4 | [name] [name] [name] [name] [name] [name] (HUSLAB) [name] (HUSLAB) | 100-150 | 50 inpatients + 50 Covid patients sick at home + 50 non-COVID controls |
| 6-12 months |  |  |  |
| Magnetic resonance imaging of the heart | HUS imaging [name], [name], [name], [name], [name] | 50 who were in intensive care, 50 who were in bed ward treatment | 50 non-COVID controls |
| Heart examination laboratory samples P- TnI, Nt -BNP, total blood count, creatinine, ECG | HUSLAB | 50 who were in intensive care, 50 who were in bed ward treatment | 50 non-COVID controls |
| 12 months |  |  |  |
| Antibody assay follow-up samples |  | 100-150 | 50 inpatients + 50 COVID patients who got sick at home |
| 24 months |  |  |  |
| Antibody assay follow-up samples |  | 100-150 | 50 inpatients + 50 COVID patients who got sick at home |
| 6 MW | physiotherapist [name] | 100-150 intensive care patients |  |
| Five years |  |  |  |
| Outpatient visits and neuropsychological testing | Intensive care clinic researchers [name], TBA | 100-150 | 50 inpatients + 50 COVID patients sick at home 50 non-COVID controls |

*Imaging*

A neuroradiologist evaluates brain magnetic resonance images for visible structural changes(e.g., infarcts and hemorrhages). Neuroradiologist [name] designs an imaging protocol suitable for the study with physicist [name] and instructs the nurse responsible for imaging logistics, [name], and is responsible for interpreting the results of MRI imaging. In addition, the physicist [name] further processes the image material in Meilahti's physicists' image laboratory (e.g., Slicer and Freesurfer), where the aim is to illustrate, e.g., damage to the olfactory nerve, damage to nerve pathways and gray/white matter atrophy. To compare the imaging findings with the results obtained in neuropsychological tests, at least 30 patients participating in MRI imaging must also be included in the neuropsychological part of the study, i.e., their language of communication should be Finnish. If coincidental findings, such as cerebral artery aneurysm or other potentially clinically important findings, are found in the magnetic resonance imaging of the brain, [name] will contact the person in charge of the study, who, together with neurologist [name], will arrange the necessary follow-up investigations and a referral to adequate treatment. Contraindications: Severe narrow space scar, heart pacemaker, metallic foreign objects in the body, or other known contraindications for MRI examination. More detailed mapping of contraindications is done according to the HUS guidelines before imaging.

Magnetic resonance imaging of the heart takes place 6-12 months after the end of hospital treatment. Cardiac radiologists [name] and [name] are responsible for cardiac magnetic resonance imaging, with specialists [name], [name], and [name], who specialize in cardiac radiology. The imaging is performed by the clinical myocarditis imaging protocol of the radiology heart imaging unit HUS Imaging with a 1.5 Tesla device. The volumes of both chambers and the ejection fraction are measured based on the volumetry of the short-axis cine images. In addition, local myocardial deformation is measured from longitudinal and short-axis images using strain methods^29^. Myocardial edema and fibrosis are measured quantitatively from T1- and T2-weighted relaxation time maps^30^. The localization and percentage of the possible left ventricular scar are determined from gadolinium-enhanced images. Subjects with troponin release during ward treatment or a myocardial scar characteristic for a previously undiagnosed myocardial infarction will be offered computed tomography (CT) of the coronary arteries at the clinical discretion of the cardiologist. However, clinical suggestions are not made if the coronary condition is known from previous examinations. Coronary arteries are assessed for the number of hemodynamically significant coronary plaques, the extensiveness of atherosclerosis, and possible coronary aneurysms, such as having been associated with coronavirus infection in children and adolescents.31 If changes are found, docent, cardiology specialist [name] programs the necessary follow-up examinations.

Exclusion criteria for cardiac magnetic resonance imaging: Permanent cardiac pacemaker or severe ischemic or other heart muscle disease already diagnosed before the illness. Contraindications: Severe claustrophobia, allergy to gadolinium or heart pacemaker. More detailed mapping of possible ferromagnetic implants and contraindications is done according to the HUS instructions before imaging each study patient.

*Smell and taste*

The examination is done in a short version, where a screening test for the sense of smell, testing the smell threshold and testing basic tastes. The research nurse does the testing at the same visit when the MRI imaging is done. The testing uses the smell screening test and the smell threshold testing of the Sniffin'Sticks (level II) test, as well as strip tests for the sense of taste. Contraindications: Known allergy to one of the odorants used and a disorder of the sense of smell diagnosed before the coronavirus infection.

*Pulmonary function and performance*

We ask the patients for consent to use the previous clinical data collected. This data includes possible spirometry and diffusing capacity studies, lung imaging, and clinical information obtained by interviewing the patient. The patients undergo standard spirometry (Pt-FV- SpirD) and diffusion capacity measurement (Pt-Dco-SB1) for the six-month follow-up outpatient clinic visit in the clinical physiology laboratory. At the outpatient clinic visit, a 6-minute walk test and measurement of oxygen saturation without supplemental oxygen are also performed before and after the walk test. Contraindications, 6-minute walk test: Severe heart disease, chest pain or severe shortness of breath during exertion, oxygen saturation in room air before the test < 90%, severe musculoskeletal disease that prevents walking or worsens during work, and febrile infection.

*Blood samples*

The following samples are taken from patients who come to the outpatient clinic with clinical indications, which are part of the routines of the outpatient clinic in the intensive care unit: total blood count, CRP, creatinine, natrium, kalium, glucose, and coagulation studies. Other blood samples are taken in the laboratory during the first clinic visit or soon after. Flow cytometry or mass spectrometry analyzes plasma and serum samples for white blood cell populations, and cytokine and antibody levels are determined. Primarily, this sub-study includes patients who have previously participated in the study "ANTIBODIES IN THE DIAGNOSTIC AND TREATMENT OF THE NEW CORONAVIRUS INFECTION (SARS-CoV-2 / COVID-19)" during their acute coronavirus infection, but also other patients with a severe disease treated in the intensive care unit. In this way, the immunological profile of the acute phase (collected earlier) in the same patients can be compared to the situation now six months after becoming ill. The research also analyzes anergy and other long-term changes in the immune system that develop as a result of severe illness. The following sample quantities and qualities are taken as research samples: 1x10 ml serum tube, 1x10 ml EDTA tube, and 4 x 10 ml heparin tube. In addition, 1x5 ml of EDTA plasma is taken for neurofilament determinations. The samples are frozen, and when the material is collected, they are sent to [name] and [name]'s laboratory in Gothenburg for analysis. For the ApoE allele determination, a 1x5ml whole blood sample is required, frozen directly to await examination. There is a separate notice and consent procedure for this sample. For fibrosis and inflammation marker analyzes (MMP-7, -8, -9, and TIMP-1 and their regulating cytokines TNFα, IL-6, IL-8, IL-10), 1x10ml of heparin plasma is collected. The samples are analyzed at the University of Tampere in the laboratory of docent [name]. To study blood coagulation properties(e.g., microvesicles related to thrombosis are analyzed, calibrated automated thrombography (CAT)), 3x 2.5ml citrate plasma is taken, which is double centrifuged and frozen for later analysis. We also ask for the subjects' consent to use the results of coagulation studies performed anonymously without clinical data from previous blood samples with HUSLAB's research permit in the research material and to combine the results with clinical data. Our partners have developed a fast and high-capacity test for measuring and studying SARS-CoV2 immunity (non-diagnostic test). The test can be used to determine 1-3 automatically with the help of artificial intelligence immunoglobulin class from the samples. The test partially corresponds to the standard immunofluorescence assay (IFA) used in routine viral diagnostics. With the help of the test, our purpose is to study which classes of antibodies against different proteins of the SARS-CoV-2 virus they express in patient samples at various stages of the infection and to examine how these correlate with the clinical picture of the disease. In addition, we find out how long antibodies are detectable in the patient's samples (samples collected at different time points) and possibly antibodies that cross-react with other coronaviruses. In the study, serum samples are taken from the patients six months, 12 months, and 24 months after hospitalization. In addition, the patients are asked for their consent to use any research samples taken from them previously, about three months after hospitalization, and also for this purpose, if the samples were taken in connection with another study. The collected samples are also tested for antibodies using other techniques (such as enzyme immunoassay (ELISA) and the microneutralization method.32, 33 The so-called avidity of the samples is also determined, i.e., how strongly the antibodies bind to the virus antigen.

The results can be used to advantage in product development work and diagnostics development in cooperation with companies in the field. If necessary, patients can be contacted again to collect additional samples. The required sample amount is 5 ml of EDTA plasma. At a separate sampling session, the time of which is determined based on the cardiac magnetic examination (the samples must be taken on the same day as the magnetic examination), the following blood samples and ECG are taken: total blood count, creatinine, biomarkers reflecting heart muscle damage and dysfunction hs-TnI and pro-BNP. Regarding antibody studies, the essential thing is to test the method and compare the test results with other methods. The tests performed are not diagnostic. The results are indicative. However, if they wish, the test subjects can know their antibody results obtained from the test, and a statement will also be given about them.

Contraindications: No contraindications

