**II Research questions, hypothesis, research goal**

The study aims to find out (Q=the question layout, H=hypothesis):

1) Q: Do patients treated in the intensive care unit due to the coronavirus show a decline in cognitive performance revealed in extensive neuropsychological tests compared to reference values determined from the general population?

H: Neuropsychological tests show changes in some patients compared to the general population of the same age group.

2) Q: Did any clinically observed neurological complications occur during intensive care?

H: Neurological complications such as delirium and cerebrovascular disorders occurred during intensive care.

3) Q: How have patients recovered from a severe illness neurologically?

H: Most of them have recovered well neurologically, but some may find symptoms in a detailed examination.

4) Q: Does the MRI examination show changes compared to the COVID-19 patients who survived without intensive care treated in the ward?

H: Patients with neurological abnormalities on clinical examination may have radiologically detectable changes on head MRI.

5) Q: Are the patients' neurological symptoms related to white matter damage that could be detected by determining neurofilament levels?

H: Patients with neurological or neurocognitive symptoms can be detected in plasma neurofilament levels compared to non-COVID patients and COVID patients who are neurologically asymptomatic.

6) Q: Is the ApoE4 allele more common in patients with severe Covid-19?

H: In intensive care and hospitalized Covid-19 patients, one or two ApoE4 alleles are detected more often than in patients with Covid-19 at home or controls who have not had a coronavirus infection.

7) Q: Do elevated neurofilament levels and any ApoE allele predict long-term neurological symptoms?

H: Patients with an elevated neurofilament level 6 months after the disease have more neuropsychological changes five years after the infection.

8) Q: Do the patients have a weakening sense of smell or taste compared to the average population 6sixmonths after becoming ill and are there any changes in the neural pathways of the sense of smell on MRI?

H: Some patients have changes in their sense of smell and taste, which have not recovered well or only partially after six months of illness. An MRI examination shows changes in the olfactory nerve or neural pathway.

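### Close-circle recruitment of non-COVID controls does not exclude blood relatives, which can attenuate the ICU versus never-infected ApoE4 contrast, one of two comparisons in question 6

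*Protocol*

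**What the plan says.** Protocol section III, in the text after the exclusion criteria, describes the never-infected controls: "We also recruited 50 control subjects who had not had a COVID-19 infection". The first source is people known to the patients, drawn "from the close circle of the subjects who gave their consent to the study". They are approached through the patients: "the subjects are asked at the follow-up clinic if there are people in their close circle who have not had COVID-19". The stated aim is that these controls be "as similar as possible to the subjects treated in the intensive care unit in terms of socioeconomic status and educational level". A second source follows: "If enough non-COVID controls are not found through this method, they can also be found among the staff of the University of Helsinki". Nothing in the text limits the close circle to spouses or friends, excludes siblings, parents or adult children, or asks for kinship to be recorded.

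Section II, question 6, sets out the comparison. For the ICU and hospitalised groups it predicts that "one or two ApoE4 alleles are detected more often than in patients with Covid-19 at home or controls who have not had a coronavirus infection". In Table 1, Visit 2, the row "Laboratory samples Fibrosis/inflammation markers Neurofilament + ApoE alleles" lists 100-150 ICU patients, with 50 ward patients, 50 COVID patients ill at home and 50 non-COVID controls.

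**The concern.** Recruiting through patients' own circles is a sensible way to balance education and social background for the cognitive outcomes. An inherited genotype is different. A sibling, parent or adult child of an ICU patient shares on average half of that patient's alleles by descent. If ApoE4 really is more common among ICU patients, it is also more common among their relatives, and a control group that contains relatives is partly matched on the exposure under study.

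A true difference between ICU patients and never-infected controls would then look smaller than it is. Adjusting for age, education or comorbidity does not undo this, because what is shared is the genotype. Related pairs also break the independence that an unpaired test assumes. If kinship is never recorded, no later analysis can remove the relatives or model the pairs.

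**Working it through.** The protocol gives no effect size, alpha or power for question 6, so there is no figure to reproduce. The check asks how far the contrast shrinks.

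**Inputs from the protocol.** Population ApoE4 carriage c0 = 15-20% (Background; read as the share of people carrying the allele); 50 non-COVID controls; 100-150 ICU patients.

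**Assumptions.** True odds ratio 2.0; Hardy-Weinberg proportions; one and two copies split among carrier patients as in the population; fraction f of controls who are first-degree relatives from 0 to 100%; two-sided alpha 0.05.

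**Step 1, allele frequency.** q = 1 - sqrt(1 - c0), p = 1 - q. This gives q = 0.078 at 15% and 0.106 at 20%.

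**Step 2, ICU carriage.** Odds = 2 × c0/(1 - c0). At 15%, odds = 0.353 and carriage c1 = 26.1%. At 20%, odds = 0.5 and c1 = 33.3%.

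**Step 3, carriage in a parent or child of an ICU patient.**
- Given a non-carrier patient: q = 0.078 (0.106 at 20%).
- Given a carrier patient: [pq(1 + q) + q²]/c0 = 0.558 (0.578 at 20%).
- At 15%: 0.739 × 0.078 + 0.261 × 0.558 = 20.3%.
- At 20%: 0.667 × 0.106 + 0.333 × 0.578 = 26.3%.

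Full siblings give 20.4% and 26.5%, practically the same. The relatives' excess is about half of the patients' excess: 5.3 of 11.1 points, and 6.3 of 13.3 points.

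**Step 4, mix the controls.** Control carriage = (1 - f) × c0 + f × (carriage in relatives). The observed odds ratio compares c1 with this.

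| First-degree relatives among controls | Control carriage (c0 = 15% / 20%) | Observed odds ratio | Loss of log odds ratio |
|---|---|---|---|
| 0% | 15.0% / 20.0% | 2.00 / 2.00 | none |
| 10% | 15.5% / 20.6% | 1.92 / 1.92 | about 6% |
| 25% | 16.3% / 21.6% | 1.81 / 1.82 | 14-15% |
| 50% | 17.7% / 23.1% | 1.65 / 1.66 | 27-28% |
| 100% | 20.3% / 26.3% | 1.38 / 1.40 | 51-53% |

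For assumed true odds ratios from 1.5 to 2.5, and for siblings as well as parents or children, the loss stays within 13-16%, 26-30% and 50-55% at 25%, 50% and 100% relatives.

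**Step 5, no true association.** If ICU carriage equals c0, relatives also carry at c0 (15.0% and 20.0%), so the contrast is not biased.

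**Step 6, power.** The normal approximation for two independent proportions, with pooled variance under the null, gives 32-42% power for 50 unrelated controls against 100-150 ICU patients. With half the controls first-degree relatives this is about 20-26%, and with all of them 11-14%. These figures ignore the correlation within related pairs.

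**The case against.** Several points on the other side stand.

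- **The share of relatives is unknown.** A close circle also contains spouses, friends and colleagues, who add no bias, and the stated aim of social and educational similarity does not call for relatives. Every non-zero row of the table is a scenario. At 10% relatives the loss is only about 6% of the log odds ratio.
- **There is another source.** University staff may be used if the first route falls short, and they dilute any effect.
- **Only one arm is touched.** A reader might infer that the whole of question 6 is compromised. The protocol does not support that. Its hypothesis also compares with COVID patients ill at home, who are recruited by newspaper and social media, and that contrast speaks most directly to severity.
- **The pull is conservative.** A reader might fear a spurious association. With no true effect this mechanism produces none.
- **The arm is weak anyway.** At 25% relatives the log odds ratio falls by about 0.10 (0.69 to 0.59), against a standard error of about 0.39 to 0.45. A null result here would say little even with unrelated controls, so it could not be put down to recruitment alone.
- **Some handling may be planned elsewhere.** Table 1 collects background information, and ApoE has its own notice and consent procedure. Neither form is shown, so a kinship question may exist. An analysis plan could also restrict the ApoE set.

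The last point answers the concern only if kinship is actually collected. The recruitment route is set in the protocol, and the text shown neither excludes relatives nor asks for the link.

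**Conclusion.** The concern holds in a limited form. As written, the recruitment route allows genetic relatives of ICU patients to serve as never-infected controls for an inherited marker. To the extent that they do, that one contrast shrinks: the difference in carriage falls by roughly half the fraction of controls who are first-degree relatives. The direction is firm. The size rests on the assumed odds ratio of 2.0, on Hardy-Weinberg proportions, and above all on an enrolment mix that the protocol does not state, so it runs from no loss to about half of the log odds ratio. The documents do not show that any relatives enrolled, and they do not justify treating this as a flaw that has to be cured before the study can answer question 6. It is a cheap improvement to one comparator arm of one question.

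**What to change.** Add one question to the control form: how the person is related to the index patient, with that patient's study code. Add one sentence to the protocol: genetic relatives of any ICU participant are left out of the ApoE4 comparison, while spouses, friends and staff controls stay in. Relatives remain in the other sub-studies, where the recorded link lets pairs be analysed as correlated. Patients can also be asked to name unrelated people first. Since the protocol describes these controls partly as already recruited, kinship can be asked afterwards where needed.

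The cost is one form item, one sentence, and a somewhat smaller ApoE control group in an arm that is already short of power. The staff route that the protocol already allows can refill it.

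### The preferred source of the only non-COVID comparator is the ICU patients' own close circle, which may bias the ICU versus non-COVID contrast on HADS, MFI-20 and RAND-36 by an unknown amount

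*Protocol*

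**What the plan says.** Protocol section III, in the recruitment text after the exclusion criteria, sets the non-COVID group at 50: "We also recruited 50 control subjects who had not had a COVID-19 infection". They are to be sought "from the close circle of the subjects who gave their consent to the study", and the stated purpose is that they be "as similar as possible to the subjects treated in the intensive care unit in terms of socioeconomic status and educational level". The patients themselves are the route, through a question put to them when they attend follow-up: "if there are people in their close circle who have not had COVID-19 and whom they would estimate would be willing to participate". Nominees receive the team's contact details and come forward themselves if they wish.

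A second route is conditional: "If enough non-COVID controls are not found through this method, they can also be found among the staff of the University of Helsinki".

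In the six-month block of Table 1, the comparators for RAND-36 are "50 inpatients + 50 COVID patients sick at home 50 + non-COVID controls". The MFI-20 and HADS rows carry ditto marks, so the same three groups apply. The six-month BRIEF-A row also lists the non-COVID controls. For the ICU group, "The assumed number of patients is around 100-150".

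The protocol does not mention strain on people close to the patient. It names no field for the control's relationship to the patient and no exclusion or adjustment for it. Background information is collected from these controls, but its content is not given.

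**The concern.** Recruiting from the close circle is sensible for outcomes that depend on education and background, such as cognitive testing. It suits anxiety, depression, fatigue and quality of life less well. A spouse or close relative has lived through the same critical illness and may be supporting the recovering patient. Matching on background in this way can also match on the stressful event whose consequences are being measured.

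If such controls score worse than comparable people without that experience, the ICU versus non-COVID difference shrinks. A real burden in the ICU group could then look smaller than it is. These outcomes matter to the project: the Background reports depression, apathy and exhaustion after intensive care, and the Ethical considerations name psychological burden and deteriorated quality of life.

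No population-norm comparison is stated for these three scales that could serve as a check. The research questions state one for cognition (question 1), smell and taste (question 8), and lung function and performance (question 9).

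**Working it through.** **No figure to reproduce.** The protocol states no effect size, SD, alpha or power for HADS, MFI-20 or RAND-36. What follows is a sensitivity range.

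**Inputs from the protocol.** ICU group 100 to 150; non-COVID controls 50.

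**Assumed inputs.**
- True ICU versus non-COVID difference d, in SD units: 0.5 or 0.8.
- Share f of the 50 controls who carry strain: 1 or 0.5.
- Their shift s: 0.1 to 0.3 SD.
- Amount h by which the control group is healthier than average through volunteering: 0 unless stated.
- Two-sided alpha 0.05.

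**Formulae.**
- Observed difference = d − f·s + h.
- SE = √(1/50 + 1/n), with n the ICU number: 0.173 for n = 100 and 0.163 for n = 150.
- Power ≈ Φ(observed/SE − 1.96).

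**Precision without bias.** The smallest difference detectable at 80% power is (1.960 + 0.842) × SE, which is 0.485 SD (n = 100) or 0.457 SD (n = 150).

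**Results for d = 0.5, h = 0.**

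| f | s | Observed | Lost (f·s/d) | Power, n = 100 | Power, n = 150 |
|---|---|---|---|---|---|
| – | 0 | 0.50 | 0% | 82.3% | 86.5% |
| 1 | 0.1 | 0.40 | 20% | 63.7% | 68.8% |
| 1 | 0.2 | 0.30 | 40% | 41.0% | 45.1% |
| 1 | 0.3 | 0.20 | 60% | 21.0% | 23.1% |
| 0.5 | 0.1 | 0.45 | 10% | 73.8% | 78.7% |
| 0.5 | 0.2 | 0.40 | 20% | 63.7% | 68.8% |
| 0.5 | 0.3 | 0.35 | 30% | 52.4% | 57.3% |

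**Larger true difference.** With d = 0.8 and f = 1, shifts of 0.1 to 0.3 SD leave 0.7 to 0.5 SD. Power stays between 82.3% and 99.0% across the two ICU sizes.

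**Opposite direction.** With d = 0.5, f = 1, s = 0.1 and h = 0.2, the observed difference is 0.5 − 0.1 + 0.2 = 0.6 SD, an overstatement. The two effects cancel when h = f·s.

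**Comparators set side by side.** Ward patients are identified through invitations to the lung clinic's follow-up. Home-COVID patients come through newspaper advertisement and social media. Neither route passes through the ICU patients' close circle, so the ICU versus ward and ICU versus home-COVID contrasts do not carry this bias. Neither can show how ICU patients differ from people without COVID-19.

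**The case against.** The strongest reply is that the harm is conjectural and that little in the protocol depends on this contrast. Several parts of it stand.

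- **One of three comparators.** A reader might take the non-COVID controls for the sole reference on these scales. Table 1 gives three groups.
- **No numbered question names these scales.** A reader might connect the issue to hypothesis 12, which mentions fatigue. That hypothesis asks whether sequelae of myocarditis on cardiac MRI lie behind fatigue and slow recovery in some patients. It is an association among patients, and the controls' fatigue scores do not enter it.
- **The make-up of the group is unknown.** A reader might infer that the controls will mostly be spouses and next of kin. The text says only close circle, which can include friends and colleagues. Requiring no past COVID-19 may remove some household members, and University staff may fill part of the 50.
- **The net direction is not settled.** A reader might infer that the ICU patients' loss is definitely understated. Controls are people thought willing, who then volunteer themselves, and this can favour healthier people.
- **Replacing the close circle has a cost.** Heavier use of University staff would work against the stated socioeconomic and educational matching, on which the cognitive tests in the same controls depend.

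The reply that this belongs in a statistical analysis plan stands only in part. Such a plan can add a sensitivity analysis, but it cannot analyse by relationship if relationship was never recorded. An offsetting bias of unknown size does not rescue the contrast either: it leaves a result that cannot be interpreted without that information.

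**Conclusion.** The concern holds as a recruitment weakness limited to one contrast. The first-choice source of the only non-COVID comparator may share the strain of the patients' illness, and nothing in the protocol would let an analyst see or remove the effect. The ICU versus non-COVID contrast on HADS, MFI-20 and RAND-36 may be biased, plausibly toward zero.

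The size cannot be stated from the protocol. Under the assumptions above, with d = 0.5 SD, the loss runs from 10% to 60% of the true difference. The upper end requires every control to carry a 0.3 SD shift, and healthy-volunteer selection could cancel or reverse any of these values. The power figures are illustrations of that assumed range and do not forecast this study. No numbered hypothesis is overturned.

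**What to change.** - Keep the close-circle route, since it serves the socioeconomic and educational matching. Instruct staff to ask patients for friends, neighbours or colleagues first, before household members or next of kin.
- Record for every non-COVID control the source (close circle or University staff) and the relationship to the patient, including whether they share a household. Ask those already enrolled.
- Report the HADS, MFI-20, RAND-36 and BRIEF-A contrasts with all non-COVID controls, and again without household or next-of-kin controls.

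**Cost.** One line in the recruitment instruction, a short addition to the data form and one extra analysis. The restricted analysis is less precise. If, for illustration, half of the 50 controls were set aside, the SE would be √(1/25 + 1/100) = 0.224 or √(1/25 + 1/150) = 0.216. The difference detectable at 80% power would rise from 0.485 to 2.802 × 0.224 = 0.63 SD (100 ICU patients), or from 0.457 to 2.802 × 0.216 = 0.61 SD (150). It should therefore be read as a check on direction and size rather than as a test. There may also be somewhat more use of the University staff route, which may match less well on education.
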